## TB035 design

[figure not shown]

### Group 1: MVA85A $5 \times 10^7$ pfu aerosol-systemic

[figure not shown]

Prior BCG

### Group 2: MVA85A $5 \times 10^7$ pfu systemic- aerosol

[figure not shown]

### Group 3: MVA85A $5 \times 10^7$ pfu systemic-systemic

[figure not shown]

Figure 1. Trial schedule  
For Group 2 amendment please see section 4.1

## 2. BACKGROUND AND RATIONALE

### 2.1 Introduction

*Mycobacterium tuberculosis* (*M. tb*) is a pathogen with worldwide preponderance which infects humans causing tuberculosis (TB), a transmissible disease resulting in very high mortality and morbidity. A third of the world's population is latently infected with *M. tb*, these people carry a 10% lifetime risk of developing active life-threatening disease (1). Worldwide there were an estimated 8.7 million new cases of TB and an estimated 1.4 million deaths associated with TB in 2011 (2). Co-infection with human immunodeficiency virus (HIV) greatly increases risk of TB reactivation and death (3, 4). Diagnosis is challenging and drug treatment can be prolonged, harmful, costly and complex. For these reasons an effective vaccine is a global public health priority.

The Bacille Calmette-Guérin (BCG) vaccine is the only licensed TB vaccine and it has been administered globally to several billion people over a 70 year period (5). Although it does not protect against pulmonary TB in many parts of the world, it is effective in preventing disseminated TB disease including tuberculous meningitis in childhood (4, 6, 7). Recently heterologous "prime-boost" vaccination strategies, in which two different candidate vaccines expressing antigens in common are given weeks or months apart, have generated strong and sustained cellular immune responses correlating with a TB protective effect in preclinical animal models. In such a "prime-boost" strategy, BCG would therefore be an ideal priming vaccine.

MVA85A is a recombinant attenuated Modified Vaccinia virus Ankara expressing the *M. tb* antigen 85A. This antigen is highly conserved in all strains of BCG and *M. tb*, and is immunodominant in both animal and human studies. Developed by the University of Oxford, MVA85A has now been administered to over 2300 human individuals with an excellent safety profile. It has been shown to be highly immunogenic as a booster vaccine in BCG-primed subjects (8). A large phase IIb efficacy trial in BCG-vaccinated infants in South Africa has recently reported no enhancement of BCG-induced protection (9), however, in this trial, the immunogenicity was significantly lower than that seen in adults, and more potent routes of administration are of interest in the field. A phase IIb trial in HIV infected adults in South Africa and Senegal is ongoing (ClinicalTrials.gov reference number NCT01151189).

To date, all new TB vaccine candidates had been administered systemically. However there is data from preclinical animal models with this and other virally vectored vaccines to suggest that immunising the respiratory mucosa may give superior protection against respiratory diseases (10-13). In addition, the aerosol inhaled route of MVA85A delivery could offer practical, tolerability and safety benefits over and above needle-based methods (see below).

A Phase I safety study assessing the safety and feasibility of administering low dose MVA85A by nebuliser direct into the airways has just been completed. To our knowledge there has been no previous clinical study of any vectored vaccine delivered by aerosol except for this completed study in our group.

Enrolment for this trial was completed in November 2012, no vaccine related Serious Adverse Events were reported and aerosol immunisation was well tolerated ([name] *et al*, personal communication). In that trial 12 volunteers have had the MVA85A as aerosol vaccination- 10 of those had the low dose ( $1 \times 10^7$  pfu) and 2 volunteers had the high dose which we would normally give intradermally ( $1 \times 10^8$  pfu). The intermediate dose of  $5 \times 10^7$  pfu will be used in this trial for the first time.

#### Rationale for the aerosol inhaled route for TB vaccination in humans

There are strong reasons for administering a TB vaccine via the airway. Preclinical animal work increasingly indicates that the best protection occurs when the route of immunisation matches the route of infection (10-12). The most common natural route of *M. tb* infection is by inhalation of

aerosolised infectious droplets containing tubercle bacilli leading to the establishment of primary infection in the lung. The lung has a distinct mucosal immune system characterised by bronchus associated lymphoid tissue (BALT) which is well adapted to encounter and process antigens presenting to the respiratory mucosa. Immunising via the airway should therefore have the advantage, over other routes of eliciting protective immune responses in the lung mucosal surface. We know that BCG, administered systemically, protects most effectively against systemic disease in childhood (6, 7). It may follow that airway vaccination is needed to induce effective protection from pulmonary disease.

The inhaled route is a well established route of drug delivery. Aerosolised droplets of bronchodilating, anti-inflammatory, and antimicrobial drugs are administered by inhalation to millions of patients each day. Clinical trials of aerosolised measles vaccines have shown that mass immunisation by the respiratory mucosal route in a developing country is feasible and can induce strong and long lasting immune responses (14-20). There is also valuable experience with aerosolised measles vaccine given to over 4 million schoolchildren in Mexico, where public acceptance was high, costs were low, and there were fewer side effects reported than with subcutaneous vaccination (21). A nasally administered influenza vaccine is licensed in North America (22-24) and others are in clinical trials (25, 26). Furthermore the principle of mucosal surface vaccination is well established as shown by those widely used in clinical practice against polio, typhoid, cholera and rotavirus.

There are numerous perceived advantages of aerosol inhaled vaccination: it is safe, needle-free, well-tolerated, popular, less technically demanding, economically beneficial, and allows self-administration of vaccine or administration by less technically trained community health workers (21). Furthermore, use of non-injectable vaccines reduces the likelihood of unsafe disposal and reuse of syringes in immunisation programmes (27).

A problem with all virally-vectored vaccines including MVA85A is that individuals build up immunity to the virus base (anti-vector immunity) which makes the vaccine less efficient and not suitable for re-use within short time frames. An important potential advantage of mucosal immunisation, in addition to the ones mentioned thus far, is that aerosol vaccination may minimise or avoid induction of systemic anti-vector immunity and allow homologous boosting with the same viral vector; thus minimising cost of vaccine development (28-30). Furthermore, for some vectors, e.g. human Adenovirus serotype-5, up to 80% of adults have antibodies to AdHu5 and this pre-existing immunity significantly limits the utility of this vector (31-34). Our hypothesis is that mucosal immunisation with MVA85A does not result in induction of systemic anti-vector immunity. Recent work in nonhuman-primates by our collaborators at the Health Protection Agency, comparing 2 routes of administration, showed anti-MVA antibody responses are seen in intradermally vaccinated animals but not in animals given MVA85A by aerosol (Figure 2; (35))

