### Anti-vaccinia Ig-G levels (arbitrary U/ml) measured in serum samples Vaccination group median (+/- SD)

[figure not shown]

**Figure 2:** Vector specific IgG response induced by vaccination with MVA85A measured by ELISA. The plot shows the median change from prevaccination level for the BCG prime with MVA85A intradermal boost group with the closed circles and for the BCG prime with MVA85A aerosol boost group with triangles. Error bars are standard deviations from the median (35).

This effect of reducing anti-vector responses by mucosal administration has also been demonstrated in mice, rabbits and guinea pigs (12, 36, 37). There is an increased need to find strategies to overcome anti-vector immunity in vaccine development especially for vaccines that will need to be given repeatedly (e.g. seasonal influenza), so if this is also demonstrated in humans, this would be an important development for the field of viral vaccines and respiratory pathogens for which mucosal immunisation may improve efficacy (11, 12).

This project will quantify for the first time the induction of anti-vector immunity (humoral and cell-mediated) by both aerosol and systemic administration of MVA85A. The functional relevance of this anti-vector immunity will be evaluated by a second boost vaccination of MVA85A via a different administration route, one month after the first, priming immunisation. This data will have implications for the TB vaccine field but also for the wider vaccine community and for the development of mucosal vaccination strategies for other respiratory and mucosal pathogens.

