## 2.2 Hypothesis

Previous studies have demonstrated that a 3 week interval between homologous MVA85A–MVA85A administered systemically does not enhance responses (8). We hypothesise that responses will be boosted in the aerosol–systemic and systemic-aerosol group but not in the systemic–systemic group.

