| Secondary Objectives
To characterise mucosal and systemic immunogenicity of viral vector (MVA) and insert (Ag85A) by comprehensive characterisation of humoral and cellular immune responses

Evaluate functional relevance of anti-vector immunity induced by aerosol and systemic immunisation in MVA85A-prime followed by homologous MVA85A-boost administered 4 weeks after the MVA85A-prime | 

1. Induction of humoral and cell-mediated immunity to MVA by aerosol and systemic immunisation

2. Induction of cell-mediated and humoral immunity to Ag85A by aerosol and systemic immunisation

3. Effect of a boosting immunisation one month after prime on humoral and cell-mediated immunity to insert (Ag85A) and vector (MVA)

 |

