# **9. STATISTICS**

## **9.1 Statistics**

This is primarily a trial with descriptive endpoints. Twelve subjects will be recruited into each arm of the trial (i.e. 36 in total). Our previous experience with clinical trials using MVA85A over the last 10 years suggests that this sample size is a feasible number to recruit, screen, enroll, and follow up in practical terms, whilst also allowing the determination of any substantial and clinically significant differences in safety and cell-mediated immunity between the three groups. A twofold increase in the magnitude of the cellular immune response (as measured by Elispot response to 85A peptide stimulation) is considered immunologically meaningful. Extrapolating effect size and variability from the completed initial aerosol vaccine safety study (TB026), twelve volunteers are needed to have 80% power to detect an immunologically meaningful difference in the summed peptide pools and 8

volunteers to achieve the same for single peptide pool of 85A. This sample size is appropriate for a proof-of-concept Phase I safety study.

It is anticipated that the immunological endpoints will not follow a normal distribution. A log transformation will be applied and if the resulting data are normally distributed they will be summarised by group using means and standard deviations. The one-week and six-month responses will be compared between the three groups using a t-test. If the resulting data are not normally distributed then medians and interquartile ranges will be used to summarise the data and the Mann Whitney U test will be used for statistical comparisons. An area-under-curve analysis will be used to compare the overall responses over time between the three groups. This analysis will make use of data collected at all time points.

Differences between means or medians between the three groups will be presented along with their 95% confidence intervals. Within each group, paired data will be analysed using either a paired t-test or the Wilcoxon matched pairs test depending on the normality of the data.

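### The hypothesis that aerosol MVA85A induces no systemic anti-vector immunity cannot be established by the analyses named in section 9.1

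*Protocol*

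**What the plan says.** The rationale for the aerosol route in Protocol section 2.1 states: "Our hypothesis is that mucosal immunisation with MVA85A does not result in induction of systemic anti-vector immunity". The trial title likewise speaks of avoiding immunity to the vector. Other text is softer. The same part of section 2.1 says "aerosol vaccination may minimise or avoid induction of systemic anti-vector immunity and allow homologous boosting with the same viral vector", and the text after Figure 2 sets an estimation aim: "This project will quantify for the first time the induction of anti-vector immunity (humoral and cell-mediated) by both aerosol and systemic administration of MVA85A".

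Section 2.2 adds a second no-effect statement: "We hypothesise that responses will be boosted in the aerosol–systemic and systemic-aerosol group but not in the systemic–systemic group". Section 3 lists "Induction of humoral and cell-mediated immunity to MVA by aerosol and systemic immunisation" as the first secondary outcome.

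Section 9.1 describes the endpoints as mainly descriptive and then names the analyses:

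- Between groups: a t-test or Mann Whitney U test at one week and six months, and an area-under-curve comparison using every time point. "Differences between means or medians between the three groups will be presented along with their 95% confidence intervals".
- Within groups: "Within each group, paired data will be analysed using either a paired t-test or the Wilcoxon matched pairs test", chosen according to normality.

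The power statement concerns the ELISPOT response to 85A, which is the insert and not the vector. Section 6.1 (Trial regimen) shows that only Group 1 is primed by aerosol and that it receives intradermal MVA85A on day 28.

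**The concern.** A hypothesis of no induction is the null hypothesis of the paired test. Failing to reject that null is not evidence for it, and the noisier the assay, the more often the test fails to reject. What bears on the claim is how large a rise the data can rule out, which is the upper confidence limit of the within-group change. Section 9.1 states no such interval and no size of rise that would count as negligible.

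At stake is the conclusion the trial may draw on one of its motivating ideas. If aerosol priming raised anti-MVA responses modestly, the named analyses could return a non-significant paired test and a clear difference from the intradermal groups. Those results would support less induction, not none. The "but not in the systemic–systemic group" part of section 2.2 has the same form.

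**Working it through.** **1. Which named analysis bears on the no-induction claim?**

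| Analysis in section 9.1 | What it can show | Can it support no induction? |
|---|---|---|
| Paired t-test or Wilcoxon, within group | That a rise occurred | No: no rise is its null, and no CI is stated |
| Between-group difference with 95% CI, before day 28 | Less induction by aerosol than by intradermal | No: it is relative to another group's rise |
| Six-month comparison | Difference after both doses | No: Group 1 has had intradermal MVA85A by then |
| Area under the curve, all time points | Difference over the whole course | No: it spans Group 1's intradermal dose |

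Group 2's aerosol dose does not help either, because it follows an intradermal prime. The clean evidence is Group 1 (n = 12) from day 0 to the pre-boost day 28 sample. Table 1 already schedules immunology bloods on days 0, 2, 7, 14 and 28.

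**2. The plan's own figure.** Section 9.1 says 12 volunteers give 80% power for a twofold difference in the summed 85A peptide pools. This cannot be reproduced, because the SD, alpha, sidedness and test are not given. Assuming a two-sided 5% test, the SD on the log10 scale that yields 80% power at n = 12 is 0.252 for a two-sample t-test and 0.339 for a paired t-test. Dividing by log10(2) = 0.301 gives about 0.84 and 1.13 on the log2 scale. Neither figure describes an anti-MVA readout.

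**3. What a non-significant paired test would leave open.** No SD for any anti-MVA change is in the protocol. I assume 0.83, 1.0 and 1.5 on the log2 scale, a range that covers the two back-solved values.

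- Standard error = SD/√12.
- Noncentrality = log2(fold)/SE, on 11 degrees of freedom, with critical value t(0.975, 11) = 2.201.
- 95% CI half-width = 2.201 × SE, back-transformed as 2^(half-width).
- A result just short of significance has its estimate one half-width above zero, so its upper limit is 2^(2 × half-width).

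Example at SD 1.0: SE = 1.0/3.464 = 0.289. For a 1.5-fold rise the noncentrality is 0.585/0.289 = 2.03, giving power 46%, so 54% are missed. The half-width is 2.201 × 0.289 = 0.635, or 1.55-fold, and the just-non-significant upper limit is 2^1.27 = 2.4-fold.

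| SD of log2 change (assumed) | 1.5-fold rise missed | Twofold rise missed | CI half-width | Upper limit when just non-significant |
|---|---|---|---|---|
| 0.83 | 40% | 3% | 1.44-fold | 2.1-fold |
| 1.0 | 54% | 12% | 1.55-fold | 2.4-fold |
| 1.5 | 77% | 44% | 1.94-fold | 3.7-fold |

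**4. Is an interval-based rule feasible with 12?** Suppose the true change is zero and the upper limit of the two-sided 95% CI must fall below a bound. By symmetry, the chance of success equals the power to detect a rise of that size. For a twofold bound it is 97%, 88% and 56% at the three SDs. For a 1.5-fold bound it is about 60%, 46% and 23%. The bounds are illustrative only. The protocol's twofold factor is stated for the 85A ELISPOT, not for anti-MVA assays.

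**The case against.** The strongest reply is that the sentence sits in the background, next to softer wording, and that the objectives speak of characterising and quantifying. The trial is mainly descriptive, the anti-vector endpoint is secondary, and section 2.2 makes a positive prediction for the aerosol–systemic group, which difference tests suit. Margins and decision rules are commonly left to a statistical analysis plan, which may exist but is not at hand.

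Much of this stands, and it limits the weight of the point. It does not remove it, because the protocol itself states the no-induction hypothesis and names the tests, and the two do not match.

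Three stronger readings should be resisted:

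- A reader might infer that a non-significant p-value will be reported as proof of absence. The protocol ties no conclusion about anti-vector immunity to any p-value.
- A reader might infer that the plan contains only difference tests. It also promises 95% intervals for between-group differences and descriptive summaries by group.
- A reader might infer that 12 volunteers are too few. That depends on an SD and a bound that the protocol does not give. Against a twofold rise, the paired test misses only 3% and 12% at two of the three assumed SDs.

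**Conclusion.** The point holds as a mismatch between a stated hypothesis and the stated analyses. As written, section 9.1 can support the conclusion that aerosol induces less anti-vector immunity than intradermal vaccine, but not that it induces none. A non-significant paired test in Group 1 would not exclude a real rise: a true 1.5-fold rise would be missed 40% to 77% of the time and a twofold rise 3% to 44%.

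These figures rest on assumed SDs of the log2 change of 0.83 to 1.5, a two-sided 5% paired t-test and 12 evaluable volunteers. The structural part of the argument needs none of those assumptions. Priority is minor: the endpoint is secondary, the trial is mainly descriptive, and the primary safety objective is unaffected.

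**What to change.** Add a short paragraph to section 9.1:

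- For Group 1, from day 0 to the pre-boost day 28 sample, report the geometric mean fold-change in anti-MVA antibody and in MVA-specific T cells with its 95% CI. Give the aerosol-minus-intradermal difference with its CI over the same window.
- Claim no meaningful induction only if the upper limit lies below a bound that the laboratory specifies in advance for those assays. Otherwise claim at most that induction is lower than intradermal, and only where the between-route interval supports it.
- Report the prediction of no boosting in Group 3 in the same way, as a within-group change with its CI.

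Alternatively, reword the section 2.1 hypothesis to say that aerosol induces less systemic anti-vector immunity than intradermal administration.

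The cost is a paragraph of text and a laboratory decision on the bound, with no new samples or volunteers. The downside is that a claim of avoiding anti-vector immunity becomes harder to make.

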### Anti-vaccinia Ig-G levels (arbitrary U/ml) measured in serum samples Vaccination group median (+/- SD)

[figure not shown]

**Figure 2:** Vector specific IgG response induced by vaccination with MVA85A measured by ELISA. The plot shows the median change from prevaccination level for the BCG prime with MVA85A intradermal boost group with the closed circles and for the BCG prime with MVA85A aerosol boost group with triangles. Error bars are standard deviations from the median (35).

This effect of reducing anti-vector responses by mucosal administration has also been demonstrated in mice, rabbits and guinea pigs (12, 36, 37). There is an increased need to find strategies to overcome anti-vector immunity in vaccine development especially for vaccines that will need to be given repeatedly (e.g. seasonal influenza), so if this is also demonstrated in humans, this would be an important development for the field of viral vaccines and respiratory pathogens for which mucosal immunisation may improve efficacy (11, 12).

This project will quantify for the first time the induction of anti-vector immunity (humoral and cell-mediated) by both aerosol and systemic administration of MVA85A. The functional relevance of this anti-vector immunity will be evaluated by a second boost vaccination of MVA85A via a different administration route, one month after the first, priming immunisation. This data will have implications for the TB vaccine field but also for the wider vaccine community and for the development of mucosal vaccination strategies for other respiratory and mucosal pathogens.

#### Description and pre-clinical experience of MVA and MVA85A

Modified vaccinia virus Ankara (MVA) is a highly attenuated strain of vaccinia virus which cannot replicate in human cells. It is known to be highly immunogenic and is therefore suitable for use as a viral vector in new vaccine development. It has an excellent safety record as it was administered intradermally to approximately 120,000 people during the smallpox eradication campaign (38-41), and has since been used in numerous clinical trials of candidate vaccines against viral, mycobacterial and protozoal infections (42, 43). Meanwhile recombinant MVA vaccines administered by respiratory mucosal and gut mucosal routes have demonstrated strong immune responses in both rodents and non-human primates (44).

Antigen 85A is a highly conserved antigen expressed by *M. tb*, BCG, and all other mycobacterial species sequenced to date. It is a 32-kDa protein, and is an enzyme, mycolyl transferase, which is involved in cell wall biosynthesis (45). Antigen 85A is highly immunodominant in both animal and

human studies (46-48), and protects against *M. tb* challenge in mice, guinea pigs and non-human primates (49, 50). The recombinant MVA85A vaccine incorporates the 1176 base pair gene for antigen 85A into the viral DNA allowing expression of this secreted antigen.

Experiments in mice, guinea pigs, cattle, and non-human primates have shown that a prime-boost schedule of vaccination with BCG followed by MVA85A, either intradermally, intramuscularly or mucosally, can improve protective efficacy against subsequent *M. tb* challenge, compared to BCG alone (10, 50-52). A mouse GLP toxicity study using the intradermal route of administration revealed no differences from PBS-injected controls apart from irritation at the site of administration. An additional mouse GLP toxicology study of aerosol administration revealed no differences from controls given aerosolised PBS.

